## Abstract

**Background:**

Secondary prevention after stroke and transient ischemic attack (TIA) is essential in order to reduce morbidity and mortality. Secondary stroke prevention studies have, however, been fairly small, or performed as clinical trials with non-representative patient selection. Long-term follow-up data is also limited. A nurse-led follow-up for risk factor improvement may be effective but the evidence is limited. The aims of this study are to perform an adequately sized, nurse-led, long-term secondary preventive follow-up with a population-based inclusion of stroke and TIA patients. The focus will be on blood pressure and lipid control as well as tobacco use and physical activity.

**Methods:**

A randomized, controlled, long-term, population-based trial with two parallel groups. The patients will be included during the initial hospital stay. Important outcome variables are sitting systolic and diastolic blood pressure, LDL cholesterol and total cholesterol. Outcomes will be measured after 12, 24 and 36 months of follow-up. Trained nurses will manage the intervention group with a focus on reaching set treatment goals as soon as possible. The control group will receive usual care. At least 200 patients will be included in each group, in order to reliably detect a difference in mean systolic blood pressure of 5 mmHg. This sample size is also adequate for detection of clinically meaningful group differences in the other outcomes.

**Discussion:**

This study will test the hypothesis that a nurse-led, long-term follow-up after stroke with a focus on reaching set treatment goals as soon as possible, is an effective secondary preventive method. If proven effective, this method could be implemented in general practice at a low cost.

**Trial registration:**

Current Controlled Trials ISRCTN23868518

## Background

The risk of stroke recurrence, myocardial infarction and death after stroke is high [1,2]. Secondary prevention after stroke is essential in order to reduce morbidity and mortality, consequently leading to reduced costs to society. There are a number of evidence based treatment strategies for secondary prevention after stroke [3]. Risk factor modification may reduce the risk of stroke recurrence by up to 80% [4]. Despite these facts, secondary stroke prevention studies have mostly been performed as clinical trials with non-representative patient selection, for example concerning age and co-morbidity [5]. There is considerable literature about non-pharmacological interventions but a paucity of data concerning the implementation of proven pharmacological interventions in patients representative of clinical praxis [6]. The number of long-term follow-up studies of secondary prevention after stroke is, to date, limited.

The implementation of risk factor intervention after stroke is difficult. There are limitations in terms of compliance and the proportion of patients achieving set treatment goals in usual care [5,7]. Even though adherence to prescribed medication may be quite high in some cohorts of stroke patients [8], the proportion achieving set treatment goals among the various risk factors has been less studied. A strategy to improve secondary prevention results by early interventions shows potential [9]. On the other hand, there is evidence that even high quality secondary preventive measures initiated while patients are hospitalized are no guarantee of a successful outcome after discharge [10]. Further research in this area is essential.

There is limited evidence that nurse-led follow up for risk factor improvement after stroke has a positive outcome [11]. In order to improve secondary prevention after stroke, we have designed a trial with the following components:

1. Population-based. All patients in the county of Jämtland, Sweden, admitted to the county hospital with transient ischemic attack (TIA) or stroke will be considered for inclusion in the study, regardless of age, gender or co-morbidity.

2. The study will be randomized with a nurse-led intervention group and a control group being seen by their general practitioner for usual medical care.

3. The intervention is based on telephone follow-ups by a stroke nurse, in order to facilitate implementation and minimize the necessary resources.

4. A routine of promptly adjusting medication in order to achieve set treatment goals for secondary stroke prevention will be established.

5. Duration of the study. A follow-up with risk factor evaluation after 12, 24 and 36 months is planned.

In this nurse-based telephone follow-up study, we hypothesized that the outcome, in terms of risk factor control, would be better in the intervention group.

Ethics approval has been received from the Ethics Committee, Umea University.

This paper presents the design of the study according to the CONSORT requirements [12].

## Methods/design

### Trial design

A randomized, controlled trial with two parallel groups and an allocation ratio of 1:1.

### Participants

All patients living in the county of Jämtland, Sweden, who were hospitalized with a diagnosis of stroke (ischemic or hemorrhagic) or TIA will be assessed for inclusion. Östersund hospital is the only hospital in the county and all patients, those in terminal care excluded, with symptoms of a suspected TIA or stroke, are referred here for diagnostic evaluation. It is a rural catchment area with a population of approximately 125,000 inhabitants. A routine for identification of all patients in the hospital with a possible TIA or stroke, based on performed brain computed tomography examinations, has been established. During a three-month test period the study nurses identified all patients with a final TIA or stroke diagnosis. All patients physically and mentally capable of communicating by telephone will be eligible. This means that patients suffering from aphasia, dementia and deafness will be excluded. The other exclusion criteria are severe, often terminal, disease, and participation in another on-going trial.

### Interventions

All eligible patients will be informed about the study and asked to give a written informed consent. They will receive standard information about stroke concerning the pathophysiology and risk factors according to established clinical praxis during their hospitalization. They will also be offered a follow-up visit to a stroke nurse and an outpatient follow-up according to normal care procedures.

Patients randomized to the intervention group will be contacted by a study nurse by phone one month after discharge. Before the call, a blood sample for lipids will be taken and a standardized blood pressure control will be performed. Blood pressure will be measured after five minutes in the sitting position and after one minute standing. The tests will be performed by a district nurse, or, for patients in the intervention group living close to the hospital, by a study nurse. Self-reported compliance with medication will be recorded. During the call the patient will be informed about the test results and whether a change in medication is necessary. Tobacco use, physical activity and dietary habits will be discussed. Smoking cessation will be encouraged and supported. Physical activity of moderate intensity for 30 minutes or more, most days of the week will be encouraged, but also adjusted to the individual patient’s capacity. Dietary advice to reduce saturated fat and increase the intake of fruit and vegetables will be given. If the patient’s cholesterol or blood pressure values are higher than anticipated, medication will be adjusted after contact from a study physician. Repeated tests will be taken within approximately four weeks and further adjustments made if necessary until target values are reached or no further changes can be considered realistic. The same routine, with an Hb1C test added, will be applied after 12, 24 and 36 months.

The target values are: blood pressure <140/<90 mmHg (optionally <130/<80 mmHg in patients at very high risk, that is, diabetic subjects), total cholesterol <4.5 mmol/l, LDL <2.5 mmol/l [13,14].

Patients randomized to the usual care group will also be contacted by phone one month following discharge after blood pressure and lipid profile have been checked. Self-reported compliance, tobacco use and physical activity will be recorded. All medical care will be given by their treating physician, usually a general practitioner, who will receive the test results (lipid profile and blood pressure), and no additional intervention will be given as a result of participation in the study. The same routine, with an Hb1C test added, will be applied after 12, 24 and 36 months, Figure 1.

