### Outcomes

Outcomes will be measured after 12, 24 and 36 months of follow-up. Outcome variables are sitting systolic and diastolic blood pressure, LDL cholesterol and total cholesterol, as well as the proportion of patients achieving the set target for these variables. Standing systolic and diastolic blood pressure, smoking rates, the proportion of patients treated with different secondary preventive drugs, diabetes control by Hb1C, change in body mass index (BMI) and physical activity will also be measured. Sitting systolic blood pressure at 36 months will be analyzed as the primary outcome. The analyses of the secondary outcomes will be exploratory.

Blood pressures measurements are standardized as described above. LDL values are calculated from the serum concentrations of cholesterol and fasting triglycerides using the Friedewald formula. Smoking (yes/no) and physical activity (duration/week) are self-reported. Deaths are available in the hospital records and will be recorded in order to detect any survival difference between groups.

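### For intervention patients living near the hospital, a study nurse who delivers the intervention may measure the primary outcome; usual care has no such option, so the assessor differs by arm for a subset

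*Protocol article*

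**What the plan says.** The Interventions section describes the intervention arm first and says who measures: a district nurse or, "for patients in the intervention group living close to the hospital, by a study nurse". The procedure is also given there: "Blood pressure will be measured after five minutes in the sitting position and after one minute standing". The one-month contact is then carried forward: "The same routine, with an Hb1C test added, will be applied after 12, 24 and 36 months".

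For the usual care group, the same section says only that patients "will also be contacted by phone one month following discharge after blood pressure and lipid profile have been checked". It does not say who does the checking. It also repeats the routine at 12, 24 and 36 months.

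The Outcomes section states: "Sitting systolic blood pressure at 36 months will be analyzed as the primary outcome". The proportion of patients reaching the target is an outcome as well. On measurement it says: "Blood pressures measurements are standardized as described above".

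On the role of the nurses, the Methods part of the Abstract says: "Trained nurses will manage the intervention group with a focus on reaching set treatment goals as soon as possible". The Interventions section has the study nurse telephone intervention patients, report their results and tell them whether medication needs to change.

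**The concern.** In a randomized comparison, the outcome should be obtained in the same way in both arms. Here the text makes the choice of assessor depend on allocation for patients who live near the hospital. In the intervention arm such a patient may be measured by a study nurse; a usual-care patient living equally close is given no such option.

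The assessor is also not neutral. A study nurse who may measure only intervention patients necessarily knows the allocation, and the same group of nurses works to bring that arm to a pressure target. The article does not use the word unblinded, but it follows from this role.

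If study nurses and district nurses obtain systematically different readings, that difference falls on one arm only. Randomization does not balance it, because it arises after allocation and because of allocation. Adjustment for gender and disability in the primary model (Statistical methods) does not remove it. Both the primary outcome and the proportion at target are exposed, and a positive or a null result would be open to a measurement explanation.

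**Working it through.** **Step 1. Does the asymmetry reach the primary outcome?** The study-nurse option is limited to the intervention arm (Interventions). That arm's routine is repeated at 36 months (Interventions). The 36-month sitting systolic pressure is primary (Outcomes). So it does.

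**Step 2. Does any stated safeguard remove it?** The standardization covers rest and posture. The sealed envelopes (Randomization) protect allocation, not measurement. The primary model adjusts for gender and disability only. None of these acts on a measurer difference.

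**Step 3. Size of the bias.** Let f be the share of the intervention arm measured by study nurses, and d the difference between study-nurse and district-nurse readings, with other patients in both arms measured in the district-nurse way. Then

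bias in the mean difference = f × d.

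The article gives neither f nor d. Both are assumed below, for illustration only.

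**Step 4. Standard error.** From Sample size: SD 19, and 180 per group as the number needed before the allowance for drop-outs.

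SE = 19 × √(2/180) = 2.00 mmHg. With the planned 200 per group, SE = 19 × √(2/200) = 1.90 mmHg.

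The stated 180 is used here only to set the standard error. It does not itself follow from the stated two-sided inputs: 2 × (1.96 + 0.84)² × 19² / 5² gives 227 per group. That is a separate matter and does not affect this point.

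**Step 5. Type I error when there is no true effect.** For a bias b,

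type I error = Φ(−1.96 + b/SE) + Φ(−1.96 − b/SE).

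| assumed f | assumed d, size (mmHg) | bias, size (mmHg) | share of 5 mmHg | type I error, 180 per group | type I error, 200 per group |
|---|---|---|---|---|---|
| any | 0 | 0 | 0% | 5.0% | 5.0% |
| 25% | 2 | 0.5 | 10% | 5.7% | 5.8% |
| 50% | 2 | 1.0 | 20% | 7.9% | 8.2% |
| 50% | 3 | 1.5 | 30% | 11.6% | 12.4% |
| 50% | 5 | 2.5 | 50% | 23.9% | 26.0% |

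The formula is symmetric in b, so the two-sided error is the same for either sign. What changes is the direction of the error. If study nurses read lower, the intervention looks better than it is. If they read higher, it looks worse: a bias of 1.0 mmHg against the intervention would turn a true 5 mmHg benefit into an expected 4 mmHg.

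**Step 6. After the fix.** With the same type of assessor in both arms, the f × d term has expectation zero and the type I error returns to 5%.

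**The case against.** The strongest reply is that the article shows a difference in who may measure, and nothing more. Most of it stands, and it limits what can be claimed.

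- A reader might infer that the bias favours the intervention, through rounding to below target or a calmer patient with a familiar nurse. The documents do not support a direction. The intervention is delivered by telephone, so it is not shown that the study nurse is more familiar to the patient than the district nurse, and other influences could raise readings.
- A reader might infer that device and place of measurement differ by arm. No section names either.
- A reader might take it as fact that district nurses measure all usual-care patients. That is a reasonable inference from the restriction of the study-nurse option to the intervention arm, but the article does not say it.
- A reader might conclude that the Outcomes section is wrong to call the measurements standardized. It refers back to the rest and posture procedure, and nothing shows that this procedure differs by arm. What differs is who may apply it.
- Only a subset of one arm is affected. The county is described as rural, and the share living close is not given.

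The objection does not remove the asymmetry itself. Nor is this a detail that an article leaves to a fuller document: the article states the rule, and the rule is tied to one arm.

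**Conclusion.** The point holds as a risk of measurement bias in the primary outcome and in the proportion at target, arising from an assessor rule that differs by arm for patients living near the hospital. That the rule exists, and that it reaches the 36-month reading, is clear from the text. That study nurses know the allocation follows from their role.

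Size and direction are not known. The illustration rests on assumed values of f and d, an SD of 19 and 180 per group. It runs from no bias, through 0.5 mmHg with type I error near 6% and 1.0 mmHg with about 8%, to 2.5 mmHg with about 24%, in either direction. These figures show what a modest measurer difference could do against a 5 mmHg design difference. They are not an estimate of bias in this trial, and the documents do not support a claim that the result is inflated in favour of the intervention.

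**What to change.** 1. Set one assessor rule for both arms at the 12-, 24- and 36-month outcome readings, for example a district nurse for every patient, and name the assessor for usual care explicitly. This makes the type of assessor equal between arms. It does not by itself blind the assessor, since the article does not say whether district nurses know the allocation.
2. State that the first scheduled reading at each time point is the outcome, not a repeat reading taken during titration. Study nurses can then still take repeat readings without touching the outcome data.
3. For outcome readings already taken by study nurses, record who measured. Add a sensitivity analysis restricted, in both arms alike, to patients not living close to the hospital, with closeness defined by the same rule in each arm. Simply dropping study-nurse readings should be avoided: it removes near-hospital patients from the intervention arm only, keeps their counterparts in usual care, and so breaks the randomized comparison.

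Cost: a short amendment. Near-hospital intervention patients would go to their district nurse for these readings, as intervention patients living elsewhere already do, so some convenience is lost. The restricted sensitivity analysis uses fewer patients and is less precise. The article gives the trial status as ongoing, so any outcome readings still to be taken can be protected.

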**Figure 1 F1:**
[figure not shown]
**Study flow chart.** BP = blood pressure measurement.

### Outcomes

Outcomes will be measured after 12, 24 and 36 months of follow-up. Outcome variables are sitting systolic and diastolic blood pressure, LDL cholesterol and total cholesterol, as well as the proportion of patients achieving the set target for these variables. Standing systolic and diastolic blood pressure, smoking rates, the proportion of patients treated with different secondary preventive drugs, diabetes control by Hb1C, change in body mass index (BMI) and physical activity will also be measured. Sitting systolic blood pressure at 36 months will be analyzed as the primary outcome. The analyses of the secondary outcomes will be exploratory.

Blood pressures measurements are standardized as described above. LDL values are calculated from the serum concentrations of cholesterol and fasting triglycerides using the Friedewald formula. Smoking (yes/no) and physical activity (duration/week) are self-reported. Deaths are available in the hospital records and will be recorded in order to detect any survival difference between groups.

### Sample size

To reliably detect a difference between groups in mean systolic blood pressure of 5 mmHg requires study groups of 180 participants (standard deviation 19, mean systolic blood pressure 140 versus 135, alpha 0.05 two-tailed, power 80%). Study groups of at least 200 participants are planned to allow for drop-outs. This sample size is also adequate for detection of clinically meaningful group differences in lipid values (0.3 mmol/l, standard deviation 1.0), smoking rates (10%), proportion reaching treatment goals (10%), change in BMI (1.0, standard deviation 4.0) and change in physical activity (10%, proportion in a given activity level), calculated with two-tailed alpha 0.05, power 80%.

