### Statistical methods

The primary analysis will be performed according to the intention-to-treat principle using a linear regression model adjusting for gender and degree of disability. The adjustment is made in order to reflect the stratified randomization process. Per protocol analyses will also be performed. Secondary outcomes will be analyzed using the primary analysis model when continuous, and using a logistic regression model, adjusting for the same covariates, when outcomes are binary. In order to assess whether there are indications of differential treatment effects across subgroups (age, gender, co-morbidity, level of education and social classification), tests for interaction will be performed, although this aim is secondary because the study is not powered for this particular purpose. Adjustment for relevant baseline covariates will be performed in additional exploratory analyses of primary and secondary outcomes in order to evaluate the effect of possible baseline imbalance. All tests will be two-sided and a *P*-value of <0.05 will be considered significant.

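### The stated inputs need 227 per group, not 180; two-sided power for 5 mmHg is about 70% at 180 evaluable per group and 75% at 200

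*Protocol article*

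**What the plan says.** The Sample size section of the protocol article gives every input to the calculation and its result: a 5 mmHg difference "requires study groups of 180 participants (standard deviation 19, mean systolic blood pressure 140 versus 135, alpha 0.05 two-tailed, power 80" per cent). It then plans a minimum of 200 per group and assigns the margin over 180 to drop-outs, without stating a drop-out rate. The abstract (Methods) justifies the 200 per group "in order to reliably detect a difference in mean systolic blood pressure of 5 mmHg". Trial design specifies "two parallel groups and an allocation ratio of 1:1". Under Outcomes, the primary outcome is the seated systolic pressure at 36 months. Statistical methods sets a linear regression adjusted for gender and degree of disability as the primary analysis, and adds: "All tests will be two-sided".

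**The concern.** The article states a sample size together with all the inputs needed to check it, and the two do not agree. Nothing has to be assumed to see this, and a condensed journal text does not explain it, because nothing is left out: the printed result does not follow from the printed inputs.

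The power of the single primary comparison is at stake. The plan accepts a 20% chance of missing a true 5 mmHg difference. If the required number is well above 180, that chance is higher than stated, the trial is less precise than its own justification says, and the abstract carries the same claim forward.

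**Working it through.** **Inputs, all from the protocol article**
- Difference: 5 mmHg, from "mean systolic blood pressure 140 versus 135" (Sample size).
- SD: 19, from "standard deviation 19" (Sample size).
- Error rates: "alpha 0.05 two-tailed, power 80" per cent (Sample size).
- Equal allocation (Trial design).
- Stated result: 180 per group. Planned enrolment: at least 200 per group.

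**Step 1: try to reproduce 180.** For two means with equal groups, n per group = 2 × (z for alpha + z for power)² × SD² / difference².

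Two-sided alpha 0.05, 80% power:
n = 2 × (1.960 + 0.842)² × 19² / 5² = 226.7, so 227. The noncentral t gives 227.6, so 228.

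The stated 180 is not reproduced. The gap is 227 − 180 = 47 per group, and 47/180 = 26%. The normal and t versions differ by one participant, so the choice between them does not explain it.

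**Step 2: look for settings that do give 180.**

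| Setting | n per group |
|---|---|
| One-sided alpha 0.05, 80% power, SD 19, normal | 2 × (1.645 + 0.842)² × 361 / 25 = 178.6, so 179 |
| The same, t-test | 179.2, so 180 |
| Two-sided alpha 0.05, 70% power, SD 19, normal | 179 |
| Two-sided alpha 0.05, 80% power, n fixed at 180 | needs SD = 5 × √(180/2) / 2.802 = 16.9 |

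**Step 3: actual power for 5 mmHg with SD 19, two-sided alpha 0.05.**
- 180 per group: standard error = 19 × √(2/180) = 2.003; 5/2.003 − 1.960 = 0.536; power 70.4% (t-test 70.2%).
- 200 per group: standard error = 19 × √(2/200) = 1.900; 5/1.900 − 1.960 = 0.672; power 74.9% (t-test 74.7%).

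The type II error is therefore about 30% at 180 (half as much again as the planned 20%) and about 25% at 200 (a quarter more).

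**Step 4: difference detectable with 80% power.** This is 2.802 × 19 × √(2/n):
- n = 180: 5.61 mmHg
- n = 200: 5.32 mmHg

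**Step 5: could the primary model's covariates close the gap?** For 180 to do the work of 227, gender and disability would together have to explain 1 − 180/227 = 21% of the outcome variance.

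**The case against.** *The planned 200 absorbs the error.* It does not. The margin over 180 is reserved for drop-outs, so it is not spare power. Even if the expectation in the Discussion that nobody is lost to follow-up were met, 200 per group gives 75%. The target is a floor, so enrolment could run higher, but nothing commits the trial to 227. What stands of this objection is that 70% should not be quoted as the one true power. It applies if exactly 180 are evaluable, and the fair statement is 70% to 75% over 180 to 200.

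*Covariate adjustment recovers the loss.* The article claims no variance reduction from gender and disability, and nothing in it supports the 21% that would be needed. Adjustment for further baseline covariates is planned only as exploratory analysis.

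A reader might think of adjusting for the one-month systolic pressure instead. The article does not support this. Patients are enrolled in hospital and randomized soon after the event, so a reading taken a month after discharge is post-randomization. For intervention patients living near the hospital, a study nurse may take it, so the measurer can differ between groups. No correlation with the 36-month value is given. Even with an assumed residual SD of 17, the formula asks for 182 per group.

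*The calculation was one-sided by mistake.* A reader might infer this from the match at 180. The BMI claim in the same section is also consistent with it: for a change of 1.0 with SD 4.0, the formula gives 252 per group two-sided and 198 one-sided. This remains an inference. The article calls its calculations two-tailed and nowhere says otherwise. A power of 70%, or an SD near 16.9, would lead to practically the same number for systolic pressure. The shortfall does not depend on its cause.

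**Conclusion.** The sample size statement is wrong as written. The printed inputs require 227 per group (228 by t-test), not 180. Two-sided power for 5 mmHg is about 70% with 180 evaluable per group and about 75% with 200 and no losses. This rests only on the article's own difference, SD, alpha and power, and on a two-group comparison without variance reduction, which is how the Sample size section presents it.

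Two stronger conclusions are not supported. The documents do not establish that a one-sided test was used in planning. They also give no ground for predicting that a null result would be misread; what follows from them is lower power and a larger detectable difference than stated.

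**What to change.** Restate the Sample size section, for example: with two-sided alpha 0.05 and SD 19, 180 to 200 evaluable participants per group give 70% to 75% power for a difference of 5 mmHg, or 80% power for a difference of 5.6 mmHg (180 per group) to 5.3 mmHg (200 per group). Change the abstract to agree, and remove from both places the claim that 5 mmHg can be reliably detected at 80% power.

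The cost is a change of wording and a less favourable stated power. The correction needs no extra participants and no change to the primary model. Raising enrolment until 80% power for 5 mmHg is reached would be a separate and much more expensive decision: if the 10% loss implied by 180/200 is assumed, 227/0.9 is about 253 per group (228/0.9 is about 254). The restatement does not depend on it.
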